### Sample size

The effect of the intervention on symptoms of depression is the primary outcome measure and this is used as starting point for the sample size calculations. Based on previous experience with this intervention in adults, we expect a Cohen’s d of 0.50. Assuming an alpha of 0.05 and a statistical power (1-beta) of 0.80, we need 50 patients in each condition. Allowing for a dropout percentage of 25% once included, we aim to recruit 126 glioma patients (63 per group) and 63 patients with haematological malignancies in total.

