### Statistical analyses

Appropriate parametric and non-parametric statistical tests will be employed to examine differences between the groups in terms of all relevant demographic and clinical variables at baseline. Missing observations at follow-up will be imputed using the multiple imputation procedure [48]. Following the CONSORT guidelines, the intention-to-treat principle will be applied. All randomized participants will be included in the analyses, regardless of how many treatment modules or sessions they complete. Within-group and between-group differences (e.g., patients with or without epileptic seizures, pain, neurological deficits, or self-reported cognitive deficits) in dependent variable scores will be analyzed using both univariate and multivariate statistical techniques. For between-group statistical comparisons, sociodemographic variables (age, gender, and education) will be used as covariates, where necessary. The effects of the interventions will be tested by means of Helmert contrasts. Relative improvements in depressive symptoms (CES-D score) in the experimental group compared with pre-treatment assessment as well as both control groups will be calculated using Cohen’s d. If the primary outcome measure is non-normally distributed, the test and the 95% confidence intervals will be based on robust standard errors and/or on non-parametric bootstrap techniques. This will help to correctly ascertain the relative effectiveness of the treatment over the control conditions.

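### The 50 patients per condition match a one-sided 5% test; read two-sided, they give about 70% power for d = 0.50, and about 67% after the allowed dropout

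*Protocol article*

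**What the plan says.** The protocol article, under Sample size, bases the calculation on the primary outcome, depressive symptoms on the CES-D. It states the effect as "Based on previous experience with this intervention in adults, we expect a Cohen’s d of 0.50" and continues: "Assuming an alpha of 0.05 and a statistical power (1-beta) of 0.80, we need 50 patients in each condition". It then adds a margin, "Allowing for a dropout percentage of 25% once included", and arrives at 63 per glioma group, 126 glioma patients in all. The section does not say whether the test is one-sided or two-sided. It names no test and credits no gain from baseline adjustment or repeated measures.

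The Statistical analyses section does not name the sidedness either. Its one pointer to a level is the fallback for a non-normal primary outcome: "the test and the 95% confidence intervals will be based on robust standard errors and/or on non-parametric bootstrap techniques". On covariates it says that "sociodemographic variables (age, gender, and education) will be used as covariates, where necessary"; baseline CES-D is not on that list. The same section plans to test intervention effects with Helmert contrasts.

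**The concern.** The section gives an effect size, an alpha, a power and a resulting number per group, so the result can be checked. With an alpha of 0.05 and nothing said about direction, most readers will assume a two-sided test, and on that assumption 50 per group is too few for the stated 80%.

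What is at stake is how a null result is read. The article presents this as the first evaluation of internet-delivered problem-solving therapy in glioma patients, so a non-significant result would carry weight. A reader who trusts the stated power would take the risk of missing a true d of 0.50 to be 20%. Read two-sided, it is about 30% with 50 evaluable per group and about 33% with the number expected after dropout. Type I error and bias are not affected.

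**Working it through.** **Inputs from the article.** d = 0.50, alpha = 0.05, power = 0.80, 50 per condition, 63 recruited per glioma group, 25% dropout (all Sample size). Allocation is 1:1, from the equal group sizes. Sidedness is not stated.

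**Step 1: reproduce the 50.** For two means with 1:1 allocation, the normal approximation is n per group = 2(z_alpha + z_power)² / d².

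- One-sided: 2(1.645 + 0.8416)² / 0.25 = 49.5, so 50. The t-test solution is 50.15, and power at 50 per group is 79.9%.
- Two-sided: 2(1.960 + 0.8416)² / 0.25 = 62.8, so 63. The t-test solution is 63.77, so 64.

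The stated figure therefore matches the one-sided calculation. The two-sided t-test figure is 14 patients per group higher (64 − 50), which is too large a gap for rounding.

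**Step 2: two-sided power with 50 per group.** The expected test statistic is d·√(n/2) = 0.5 × √25 = 2.50. The normal approximation gives Φ(2.50 − 1.96) = 70.5%; the t-test gives 69.7%. The effect detectable with 80% power is d = 0.57 (0.566).

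**Step 3: the number expected after dropout.** The 63 equals 50 × 1.25. With 25% lost, 63 × 0.75 = 47.25, so about 47 per group remain. Then 0.5 × √23.5 = 2.42, and the normal approximation gives 67.9%; the t-test gives 66.9%. The effect detectable with 80% power is d = 0.58.

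**Step 4: could baseline adjustment support 50?** A two-sided ANCOVA on baseline CES-D multiplies the residual variance by 1 − r², so the effective d is 0.50/√(1 − r²). The article gives no r, so these values are assumptions shown as a range:

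| Assumed r | Power, 50 per group | Power, 47 per group |
|---|---|---|
| 0 (unadjusted) | 70% | 67% |
| 0.3 | 74% | 71% |
| 0.45 | 79% | 77% |
| 0.5 | 82% | 79% |

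On the normal approximation, 62.79 × (1 − 0.45²) = 50.1, so a correlation near 0.45 would bring the two-sided requirement down to about 50.

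**Step 5: could a Helmert contrast support 50?** Take one group against the mean of the other two, with 50 in each of three groups and the contrast itself equal to 0.50. The standard error in SD units is √(1/50 + 1/100) = 0.173, the expected statistic is 0.50/0.173 = 2.89, and two-sided power is 81.8%.

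**The case against.** The strongest reply is that no error is proven. Sidedness is unstated, a one-sided 5% test reproduces the 50, and the confidence-interval sentence applies only if the outcome is non-normal. This stands in part: two-sidedness is an inference. The condition, however, concerns how the interval is computed, not its level. A one-sided 5% test corresponds to a 90% interval, and the article nowhere declares a directional test. If one was intended, the paragraph still has to say so.

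A reader might also infer that the 80% can hold under a one-sided test and in no other way. The documents do not support that. The sample size section names no test, and both a two-sided ANCOVA with r around 0.45 to 0.5 and a one-versus-two Helmert contrast give about 80% with 50 per group. Neither is stated as the basis of the 50, though. The ANCOVA needs a covariate that the article does not list and a correlation that it does not give. The contrast needs 0.50 to be the difference from the pooled controls, and the haematological patients, for whom the course is also adapted, would have to serve as controls. These routes limit the claim to the unadjusted pairwise comparison; they do not justify the paragraph.

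It can also be said that all randomised patients are analysed, with multiple imputation. That keeps everyone in the analysis but does not in general restore the information lost to dropout. The 63 per group would give about 80% two-sided (79.5% by t-test) only if nobody were lost.

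**Conclusion.** The point holds in this form. For an unadjusted two-group comparison with the stated inputs, 50 per condition is the one-sided 5% figure. Under the usual two-sided reading, 64 evaluable per group are needed. Power for d = 0.50 is then about 70% with 50 evaluable and about 67% with the roughly 47 expected after dropout, and 80% power is reached only for d = 0.57 and d = 0.58 respectively.

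This rests on two assumptions: that the test is two-sided, which the article implies but does not state, and that the comparison is unadjusted, since no variance reduction is declared. A reader might call it a plain arithmetic mistake. The text does not establish that, because an undeclared one-sided test explains the figure equally well. Either way, the stated power cannot be relied on until the sidedness and the analysis behind it are given.

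**What to change.** Rewrite the sample size paragraph; no extra enrolment is required. One of two forms will do.

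1. State that the primary test is two-sided at 0.05, and give the power for d = 0.50 as about 70% with 50 evaluable per group and about 67% with the roughly 47 expected from 63 after 25% dropout. Add the effects detectable with 80% power, d = 0.57 and d = 0.58.
2. Prespecify a two-sided ANCOVA on baseline CES-D, which is already collected, and give its power with the correlation labelled as an assumption: with 47 per group, about 71% at r = 0.3 and 79% at r = 0.5; with 50 per group, 74% and 82%.

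The cost is one paragraph and, in the first form, a less favourable stated power. The second form also adds one covariate to the analysis section, and it should be fixed before outcome data are examined; the article says the trial is still recruiting. If the sponsor prefers to keep 80% two-sided without adjustment, the target is 64 evaluable per group, or 64/0.75 = 85.3, so 86 recruited per group and 172 glioma patients. That is an option, not a requirement of this correction.

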**Methods/design:**

The intervention is based on problem-solving therapy. An existing 5-week course is adapted for use by adult glioma patients with mild to moderate depressive symptoms (Center for Epidemiology Studies Depression Scale score ≥12). Sample size calculations yield 126 glioma patients to be included, who are randomly assigned to either the intervention group or a waiting list control group. In addition, we aim to include 63 patients with haematological cancer in a non-central nervous system malignancy control group. Assessments take place at baseline, after 6 and 12 weeks, and after 6 and 12 months. Primary outcome measure is the change in depressive symptoms. Secondary outcome measures include health-related quality of life, fatigue, costs and patient satisfaction. In addition, all patients are asked to assign a primary informal caregiver, who does not participate in the intervention but who is asked to complete similar assessments. Their mood, health-related quality of life and fatigue is evaluated as well.

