## Discussion

In this paper, we describe the study design of a randomized controlled trial aimed at evaluating the effects of an internet-based, guided self-help intervention for depressive symptoms in glioma patients. This study is innovative in two ways: 1) as of yet, there is no evidence from RCTs for the effectiveness of psychotherapy in glioma patients with depressive symptoms; and 2) to our knowledge, providing psychosocial care through the internet has not been explored in the depressed glioma patient population until now.

We expect the external validity of this study to be high, as we employ only few exclusion criteria. Any adult WHO grade II, III or IV glioma patient at any disease stage with mild depressive symptoms is invited to participate in the trial to try and relief these symptoms. Furthermore, as the intervention is administered through the internet and patient inclusion is organized nation-wide, we should be able to reach a large group of potential participants. Using the internet also evidently has its downsides. For certain patients, such as those unaccustomed to using the computer in their everyday lives or those with more severe cognitive impairment, using the internet may prove more difficult and could possibly result in non-participation or dropout of the study. We aim to construct the website in a very straightforward and easy-to-use way, in order to minimize this possibly negative effect. In addition, both interventions using the internet and self-help interventions are prone to high dropout rates [49], suggesting that this problem could occur in our trial as well. Therefore we present the online questionnaires separately from the intervention website, and email reminders are sent for both the assessments and the course assignments separately. Moreover, if participants do not respond to these reminders, we try and contact them through telephone instead. This should strengthen the relationship between the participants and the researchers substantially, thereby possibly improving patient participation throughout the trial [50].

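### The target of 63 per group does not cover the stated 25% dropout: about 47 completers are expected per group, not the 50 required (minor arithmetic error)

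*Protocol article*

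**What the plan says.** The Sample size section builds the target in two steps.

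- **Requirement.** The effect size is given as "we expect a Cohen’s d of 0.50". With "Assuming an alpha of 0.05" and "a statistical power (1-beta) of 0.80", the article concludes "we need 50 patients in each condition". It does not say whether the test is one-sided or two-sided.
- **Allowance.** The section continues: "Allowing for a dropout percentage of 25% once included, we aim to recruit 126 glioma patients (63 per group"). The haematological control group gets the same figure of 63.

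The Abstract repeats the result: "Sample size calculations yield 126 glioma patients to be included", again with 63 haematological patients.

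Two other sections bear on the point. Statistical analyses applies intention-to-treat to all randomized participants and uses multiple imputation for missing follow-up. The Discussion cautions that "both interventions using the internet and self-help interventions are prone to high dropout rates" and then lists countermeasures: questionnaires kept apart from the intervention website, e-mail reminders and telephone contact.

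**The concern.** Three printed figures have to fit together: the requirement (50), the dropout rate (25%) and the target (63). The words "Allowing for a dropout percentage of 25% once included" make the 25% a share of the patients who enter, so three quarters of the target should be at least 50. It is not. The target looks as if 25% of the requirement had been added, which is a smaller allowance than the one described.

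At stake is whether the recruitment target delivers the number that the plan says it needs for the primary outcome. The Discussion's caution about dropout does not repeat the error, but it shows that the allowance may well be used in full.

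**Working it through.** **Inputs**, all from the Sample size section: d = 0.50; alpha 0.05 (sidedness not stated); power 0.80; 50 needed per condition; 25% dropout of those included; target 63 per group.

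**1. Reproducing the 50.** Normal approximation: n per group = 2(z_alpha + z_beta)^2 / d^2.

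- One-sided: 2 x (1.645 + 0.842)^2 / 0.25 = 49.5, so 50 (t-test: 50.2).
- Two-sided: 2 x (1.960 + 0.842)^2 / 0.25 = 62.8, so 63 (t-test: 63.8).

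The stated 50 reproduces only on a one-sided basis.

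**2. Reproducing the 63.**

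- Adding 25% of the requirement: 50 x 1.25 = 62.5, rounded up to 63. This matches.
- Dividing by the proportion retained: 50 / 0.75 = 66.7, rounded up to 67. This does not match.

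The article prints no inflation formula, so multiplication by 1.25 is an inference. The next step does not depend on it.

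**3. What 63 delivers at 25% dropout.**

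- Per group: 63 x 0.75 = 47.25, about 47 completers.
- Both glioma groups: 126 x 0.75 = 94.5, against 100 needed.
- Haematological group: also 47.25 of 63.
- Dropout that still leaves 50: 1 - 50/63 = 20.6%, or 13 patients per group.
- Check of the alternative: 67 x 0.75 = 50.25, which is at least 50.

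**4. What the shortfall costs.** Two-sample t-test in completers, d = 0.50, alpha 0.05:

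| Completers per group | Power, one-sided | Power, two-sided |
|---|---|---|
| 50 | 0.799 | 0.697 |
| 47 | 0.777 | 0.669 |
| Loss | 0.022 | 0.028 |

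The effect detectable with 80% power moves from 0.501 to 0.517 one-sided, or from 0.566 to 0.584 two-sided. Either way the change is about 0.02 in d.

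**The case against.** **Everyone is analysed.** Statistical analyses keeps all randomized participants and imputes missing follow-up, so 47 is not the number analysed. That is correct: 47 is the expected number of completers, and the powers above are complete-case figures. The inconsistency remains, because imputation does not in general restore the information lost with a missing outcome, and because the plan itself adds patients for dropout on top of the 50.

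**63 is also the two-sided requirement.** This is true numerically, but the article derives 63 from 50 plus dropout. Read the other way, 63 would contain no dropout allowance at all.

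**Allowing for 25% might mean adding 25%.** The arithmetic would then be as intended, but the dropout covered would be 20.6%. The wording ties the 25% to patients already included.

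**The shortfall is small.** This stands. It is about three completers per group, or four recruits, and no test, estimand or analysis set changes.

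**A stronger reading a reader might infer** is that the dropout error brings power down to 67%. The documents do not support that. Of the gap between 0.80 and 0.669 two-sided, the step from 0.80 to 0.697 is already there at the full 50 and comes from sidedness. Only the step from 0.697 to 0.669 belongs to the dropout allowance.

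**Conclusion.** The statement is wrong as written, and the error is minor. At the plan's own dropout rate, 63 per group leaves about 47 completers instead of 50, and the target covers dropout of at most 20.6%. Taken alone, this costs 2 to 3 points of power at d = 0.50.

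The conclusion that 63 is too few for 50 completers rests only on the three printed figures and on reading the 25% as a share of those included. The power figures also assume a two-sample t-test in completers.

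Two further inferences go beyond the documents. First, 67 per group is not established as the right target. It follows only if 50 is the right requirement; if the test is two-sided, the requirement before dropout is 63 to 64, which becomes 84 to 86 after division by 0.75. Second, no credit for adjusting for baseline CES-D can be quantified, because the article gives no baseline correlation and names only age, gender and education as covariates.

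**What to change.** Restate the Sample size paragraph along these lines:

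> A target of 63 per group retains 50 completers only if dropout is at most 20.6%. At 25% dropout, about 47 per group are expected to complete, which gives a power of [0.777 one-sided / 0.669 two-sided] for d = 0.50 in a t-test of completers.

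Keep the alternative that matches the planned test and state its sidedness. Apply the same correction to the haematological group. The Abstract totals can stay if the target is unchanged.

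This costs a change of text and no patients. If the sponsor prefers to keep 50 completers after 25% dropout, the corresponding target is 67 per group: 134 glioma patients instead of 126, and 201 in all instead of 189 (3 x 67 against 3 x 63), with the Abstract changed to match. That is four more patients per group. The Discussion places the trial in recruitment, so the target could still be changed. Settle sidedness first, because 67 holds only if the 50 does.

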## Methods/design

### Design

This study is a randomized controlled trial evaluating the effects of an internet-based guided self-help course for depressive symptoms in glioma patients. We compare a group of patients who receive the intervention with a three month waiting list control group and a non-central nervous system malignancy control group. The intervention, which takes approximately 5 weeks to complete, is aimed at patients with mild to moderate depressive symptoms.

Assessments include self-reported outcomes completed online. The assessments are scheduled at baseline (T0), after completion of the online course (approximately 6 weeks after baseline; T1), 12 weeks after baseline (T2), and 12 months after baseline, see Figure 1. Those in the waiting list control group receive the same assessments, but are also assessed after completion of the online course (T3; approximately 6 weeks after T2), and 12 weeks thereafter (T4). Furthermore, patients with a high-grade malignancy undergo an additional assessment at 6 months after baseline (T3 or T5), as is also depicted in Figure 1. This study is performed in accordance with the Declaration of Helsinki.

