### Intervention

The internet-based guided self-help intervention is based on the principles of problem solving therapy. The original intervention, ‘Everything under control’ (“*Alles onder controle*”) has been shown to have significant positive effects on depression, anxiety and stress/burnout in a randomized controlled trial with 215 adults from the general population [39]. With small changes, this online intervention is adapted for use by glioma patients and patients with haematological malignancies. Modifications concern additional information about the specific diseases and their treatment, and the psychological impact on everyday life. Examples of participants’ assignments are made disease-specific.

The intervention consists of 5 modules with text and exercises. Patients are asked to complete one module a week and spend a minimum of two hours a week on their exercises. During the intervention, patients describe what they feel is important in their lives, make a list of their problems and concerns, and divide these into three categories: 1) unimportant problems (problems that are not related to what is important in their life), 2) important and solvable, and 3) important but unsolvable. For each of these problems the patient makes a plan on how to cope with this, guided by methods explained in the modules. The participants receive feedback on the exercises from a personal coach within three working days after completion of the assignment. The coach is not a therapist, but only supports the patient in working through the intervention. Participants can always contact their coach for additional support through the website. The coaching is provided by one of the researchers ([name]), by trained and supervised students in the final phase of a Master’s program in Psychology or by specialists from Prezens. In collaboration with the VU University medical center, Prezens provides psychological care and support.

The glioma patients in the waiting list control group are offered the same intervention after completion of the 12 weeks follow-up (T2).

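### The non-randomised haematological group is recruited at the size of a randomised arm and treated as a control for effectiveness, but no effect size fits that comparison and its Cohen's d is not a treatment effect

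*Protocol article*

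**What the plan says.** The Sample size section starts from the course's effect on depressive symptoms: "The effect of the intervention on symptoms of depression is the primary outcome measure and this is used as starting point for the sample size". It states "Based on previous experience with this intervention in adults, we expect a Cohen’s d of 0.50" and "Assuming an alpha of 0.05 and a statistical power (1-beta) of 0.80, we need 50 patients in each condition". After a 25% dropout allowance it concludes that "we aim to recruit 126 glioma patients (63 per group) and 63 patients with haematological malignancies in total". The haematological number equals that of each randomised glioma arm, and no separate effect size or rationale is given for it.

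The Randomization section allocates glioma patients only.

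On what the haematological patients receive, the article points two ways. The Intervention section says that "this online intervention is adapted for use by glioma patients and patients with haematological malignancies", and describes a deferred offer only for the glioma waiting list. The Design section compares a "group of patients who receive the intervention with a three month waiting list control group and a non-central nervous system malignancy control group", which sets the treated group apart from both controls.

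The Statistical analyses section plans Cohen's d for improvement "in the experimental group compared with pre-treatment assessment as well as both control groups". It closes the paragraph with "This will help to correctly ascertain the relative effectiveness of the treatment over the control conditions".

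**The concern.** A d of 0.50 taken from experience with the course describes what the course adds over not having it. It is not an expected difference between glioma and haematological patients, and the article gives no figure for that difference. Yet the haematological group has the same size as a randomised arm and is listed with the waiting list as a control over which effectiveness is judged.

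Two misreadings follow. A d near 0 against this group could be reported as no benefit over a control condition when the course had worked equally well in both diseases. A d away from 0 could be credited to the course when it reflects differences between the diseases. Nor could a null result be taken as showing that the course works as well in glioma, because the estimate is too imprecise.

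**Working it through.** **Inputs.** From Sample size: d = 0.50, alpha 0.05 (sidedness not stated), power 0.80, 50 per condition, 25% dropout, 63 recruited per group. The expected glioma–haematological difference is not given, so the values used for it below are assumptions.

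**1. The plan's own figure.** n per group = 2(z_alpha + z_beta)²/d².
- One-sided: 2(1.645 + 0.842)²/0.25 = 49.5, so 50. This reproduces the stated number.
- Two-sided: 2(1.960 + 0.842)²/0.25 = 62.8, so 63. This does not.
- At n = 50 and d = 0.50, t-test power is 80% one-sided and 70% two-sided.
- Recruitment: 50 × 1.25 = 62.5, so 63. With 25% loss, 63 × 0.75 = 47 complete.

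Because the stated 50 matches a one-sided test, both bases are shown below.

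**2. What d against the haematological group estimates.**

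| Exposure of the haematological group | What d measures | Expected value |
|---|---|---|
| Takes the course | Between-disease difference in response | 0.50 − 0.50 = 0 if the course works equally in both |
| Does not take the course | Course effect mixed with disease differences | Not determined by the course effect alone, since allocation is by diagnosis |

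If the group is treated, a true difference of 0.50 would need a haematological effect of about 0 or about 1.0.

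**3. Power for assumed true differences** (two-sample t-test, alpha 0.05, 50 per group).

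| Assumed difference (SD) | Two-sided | One-sided |
|---|---|---|
| 0.10 | 7.9% | 12.5% |
| 0.25 | 23.6% | 34.3% |
| 0.40 | 50.8% | 63.4% |
| 0.50 | 69.7% | 79.9% |

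With 47 completers per group, the smallest difference detectable with 80% power is 0.58 two-sided or 0.52 one-sided.

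**4. Precision.** The 95% CI half-width in SD units is t(0.975, 2n − 2) × √(2/n).
- n = 50: 0.397.
- n = 47: 0.410.

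An observed difference of 0 would therefore leave open a shortfall of about 0.40, which is 0.397/0.50 = 79% of the assumed course effect.

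**5. Possible reach into the main test.** The plan tests effects with Helmert contrasts and does not give their order. Assume that one contrast sets glioma intervention against the mean of both controls, with 47 per group and SE = √(1.5/47) = 0.179.
- Haematological effect 0: contrast 0.50, two-sided power 80%.
- Haematological effect 0.50: contrast 0.50 − (0 + 0.50)/2 = 0.25, two-sided power 29%.

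This applies only under that assumed order.

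**The case against.** A reader might infer something stronger: that the haematological group is definitely given the course, and that the plan claims 80% power for comparing glioma with haematological patients and falls far short of it. The documents do not support either part.

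- **Exposure.** No sentence says that this group receives the course, or when. It is a strong inference: the content is adapted for them, deferral is described only for the glioma waiting list, and only the waiting list has a shifted assessment schedule. The Design section nevertheless reads the other way, and the participant-flow figure is not available here.
- **Power claim.** The abstract ties the calculation to the 126 glioma patients and presents the 63 haematological patients as an additional aim. Matching a disease-control group to the arm size is an ordinary choice. That the 63 was derived from d = 0.50 for this comparison is inferred from the equal numbers and the reference to each condition.
- **Like with like.** Setting two-sided power against the stated 80% would mix bases, because 50 per group reaches 80% only one-sided. The 5% rejection rate at a true difference of 0 is simply alpha, not a loss of power.

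It can also be said that the closing sentence of the analysis paragraph follows the sentence on robust standard errors and bootstrap intervals and may refer to those, and that a non-CNS malignancy control is recognisably a disease control. This does not remove the problem. The plural in that sentence, and the planned d against both control groups, still place a non-randomised and probably treated cohort beside the waiting list as a yardstick for effectiveness.

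**Conclusion.** The point holds as a matter of interpretation and sizing for a secondary, non-randomised comparison. On either reading of the haematological group's exposure, Cohen's d against it does not measure the effectiveness of the course, and nothing in the article supports d = 0.50 with 80% power for it. The power values rest on assumed differences and an unadjusted two-sample comparison. The CI half-width of about 0.40 SD (0.41 with 47 completers) does not depend on the assumed difference.

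The randomised comparison of glioma intervention with glioma waiting list is unaffected, unless the Helmert coding pools the haematological group with the waiting list. The point should be corrected because, followed as written, the plan could lead to a wrong conclusion about effectiveness.

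**What to change.** 1. Reconcile the Design and Intervention sections on whether and when the haematological group receives the course.
2. In Sample size, state that d = 0.50 and 80% power refer only to glioma intervention versus glioma waiting list. For the haematological comparison, give the expected precision instead: a 95% CI of about ±0.4 SD.
3. In Statistical analyses, base effectiveness claims on the randomised waiting-list comparison alone, and do not pool the haematological group with the waiting list in any contrast. Report the haematological group as a non-randomised between-disease comparison, with a 95% CI.

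The cost is wording in the protocol and analysis plan, with no extra patients or data. The downside is a less favourable statement of what the haematological comparison can show.
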